**7-6-2. Phase Ib part**

20 cases if performed in 1 group

In case of 2 groups, 20 cases in each group, 40 cases in total

＜Rationale for setting the dose>

In order to determine the recommended dose for Phase II and beyond, 20 cases per group was set based on the number of cases in which the effect of regulatory T-cell removal can be studied and the feasibility of case enrollment.

**7-7. Dosing methods**

When administering the drug, ensure that the drug meets the "7-7-1. Administration Criteria" and does not conflict with the "7-7-2. Postponement of Administration Criteria" and "7-7-3. Criteria for discontinuation of administration”.

The investigational drug must be started within 2 weeks of case enrollment.

[Phase Ia] Either 0.1 mg/kg, 0.5 mg/kg or 1.0 mg/kg dose is administered intravenously over 2 hours once a week for a total of 8 doses.

[Phase Ib] If tolerability up to 1.0 mg/kg was confirmed in Phase Ia, 0.1 mg/kg or 1.0 mg/kg18

or 0.1 mg/kg or 0.5 mg/kg if tolerability up to 0.5 mg/kg is confirmed, or 0.1 mg/kg if tolerability up to 0.1 mg/kg is confirmed, administered intravenously over 2 hours once a week for a total of 8 doses.

[Common to both Phase Ia and Phase Ib]

1) Maintenance dose

The ninth and subsequent doses of the investigational drug will be administered every 4 weeks as maintenance doses, provided that "7-8. Criteria for Drug Discontinuation" are not violated.

2) Dosing Interval

The dosing interval should not be shortened until 8 doses have been administered. After the 9th dose, dosing may be postponed for up to 2 weeks, and the next dose may be shortened by up to 2 weeks.

3) Pre-treatment at the time of administration

Since reactions associated with injection are expected to occur in almost all patients, 30 to 50 mg of diphenhydramine and 300 to 500 mg of acetaminophen should be taken 30 minutes prior to administration of the study drug. In addition, 100 mg of hydrocortisone should be administered intravenously before the second dose of diphenhydramine 30-50 mg and 300-500 mg of acetaminophen after the first dose. Dosage may be adjusted according to age and symptoms.

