**5. Dosing regimen**

When administering the drug, make sure that the "7-7-1. Dosing criteria" are met and that the "7-7-2. Dosing deferment criteria" and "7-7-3. Dosing discontinuation criteria" are not violated.

【Phase Ia】 Either 0.1 mg/kg, 0.5 mg/kg or 1.0 mg/kg is administered intravenously over 2 hours once a week for a total of eight doses.

【Phase Ib】 Either 0.1 mg/kg or 1.0 mg if tolerated up to 1.0 mg/kg in Phase Ia, either 0.1 mg/kg or 0.5 mg/kg if tolerated up to 0.5 mg/kg, or 0.1 mg/kg intravenously over 2 hours once a week for a total of 8 doses.

【Common to Phase Ia and Phase Ib】

1) Maintenance dose

The ninth and subsequent doses may be administered if the study drug meets the criteria for maintenance dosing described in 7-8, and maintenance dosing should be conducted every 4 weeks. Criteria for Drug Discontinuation".

2) Dosing interval

The dosing interval should not be shortened until eight doses have been administered. After nine doses, dosing may be postponed for up to two weeks and the next dose may be shortened by up to two weeks.

3) Pre-treatment at the time of administration

As reactions to injection are expected in almost all patients, diphenhydramine 30-50 mg and acetaminophen 300-500 mg should be taken internally 30 minutes before administration of the study drug. Hydrocortisone 100 mg is also administered intravenously pre-dose; after the second dose, diphenhydramine 30-50 mg and acetaminophen 300-500 mg are administered pre-dose. Drugs or doses may be changed or increased or decreased as appropriate according to age, symptoms and other factors.

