**4-1. Selection criteria for patients**

Patients with advanced or recurrent solid tumors who meet all of the following criteria at the time of enrollment will be eligible.

1) Patients whose tumor cells are negative for CCR4 expression (diagnosis should be made using a method commercialized in Japan) and whose histopathological diagnosis of malignancy such as lung cancer, gastric cancer, esophageal cancer, malignant melanoma, or ovarian cancer is confirmed.

2) Patients who are refractory or intolerant to standard treatment, have no appropriate treatment, or have refused standard treatment.

3) Patients with a performance status (ECOG criteria) of 0, 1, or 2

4) Patients must be at least 20 years of age on the date of obtaining consent to participate in the clinical trial.

5) No severe damage to major organs (bone marrow, heart, lungs, liver, kidney, etc.) and laboratory values (within 2 weeks prior to enrollment) that meet the following criteria

Neutrophil count: 1,500/μL or more

Hemoglobin level: 8.0 g/dL or higher

Platelet count: 75,000/μL or higher

Serum total bilirubin level: 2.0 mg/dL or less

AST (GOT), ALT (GPT): not more than 2.5 times the upper limit of the facility standard (not more than 5.0 times the upper limit of the facility standard if the cause is judged to be hepatic infiltration due to the primary disease)

Serum creatinine: 1.5 mg/dL or less

Arterial blood oxygen saturation: 93% or higher (room temperature)

Electrocardiogram: No abnormal findings requiring treatment

Left heart ejection fraction (by echocardiography): 50% or more

6) The patient must agree to use a condom or other contraceptive method from the time of consent until 24 weeks after completion of study drug administration (excluding postmenopausal women (more than 1 year after the last menstrual period) or women who have undergone surgical sterilization and men who have undergone surgical sterilization)

7) The patient has given written consent.

8) Patients who are able to be hospitalized for the administration of Mogamulizumab from before the first dose until the day after the first dose.

9) Patients with measurable lesions in RECIST ver. 1.1 (New response evaluation criteria in solid tumours:Revised RECIST guideline (version 1.1)^12)^. Patients must have measurable disease at

10) Expected survival of at least 3 months.

<Rationale for setting>

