1) To confirm the clinical efficacy of the drug in eliminating regulatory T cells, and to confirm that the patients have pathologically eligible tumors.

2) To select patients for whom there are no medical or ethical problems in administering the investigational drug.

3) The selection criteria were set to select patients with general conditions that would not interfere with participation in the clinical trial.

4) The age was set as the age at which consent can be obtained from the patient himself/herself.

5) The age was set to select patients for whom safety can be ensured.

6) The safety of the investigational drug for the fetus has not been established.

7) The selection was made in order to select patients whose consent was appropriately obtained.

8) Established to ensure the safety of subjects in the event of an injection-related reaction.

9) To select patients for whom the efficacy of the investigational drug can be evaluated.

10) The selection was made to evaluate the safety and efficacy of repeated administration of the investigational drug, and to select patients who are expected to survive for at least 3 months or longer.

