**7-9. Pre-treatment and concomitant therapy**

Confirm that no prior therapy (chemotherapy, radiotherapy, etc.) has been given for the subject's disease within 4 weeks prior to the start of the study. Immunotherapy (tumor vaccine, etc.) must not have been administered within 12 weeks prior to case enrollment. Confirm that there are no exclusion criteria.

Anticancer agents, immunosuppressive agents (excluding steroids), immunoenhancing agents, radiation therapy, and surgery for the primary disease (including metastasized tumors) are prohibited during the period of study drug administration. Corticosteroids may be administered locally or systemically as pretreatment for administration of the investigational drug or for symptomatic improvement of complications and adverse events.

Intravenous infusion of zoledronic acid or pamidronate and subcutaneous injection of denosumab for bone metastases are allowed if they have been administered once every 4 weeks if they were continued prior to participation in this study. However, they should not be administered on the same day as the investigational drug.

The following vaccines should be administered concomitantly.

1. Inactivated vaccines [may attenuate the effect of the vaccine (response to vaccination is unknown)].

2. Live or attenuated live vaccines [appropriate measures should be taken if symptoms based on the original disease of the live vaccine inoculated develop (response to vaccination is unknown, and secondary infection by live vaccine cannot be ruled out)]. Treatment for other complications and adverse events should be available. Unapproved drugs and alternative therapies (e.g., folk remedies) are prohibited, but the use of food-like supplements is not prohibited.

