**8-3. Definition of evaluation items**

**8-3-1. Definition of primary evaluation items**

1) Phase Ia

(1) Safety

The maximum tolerated dose (MTD) and dose-limiting toxicity (DLT) will be determined, and the type, frequency, and severity of adverse events will be observed. The Common Terminology Criteria for Adverse Events (CTCAE) v4.0 Japanese translation of the JCOG version^13)^ will be used for grading adverse events. Adverse events will be graded according to CTCAE v4.0.

The MTD is defined as the dose at which the number of subjects who developed DLT during the period up to 28 days after the start of treatment with the investigational drug was 3 or more. However, if the MTD is not reached at any dose, 1.0 mg/kg shall be the dose that was found to be well tolerated.

The observation period for DLT will be up to 28 days after the start of study drug administration. Among adverse events for which a causal relationship to the investigational drug cannot be ruled out, the following events will be considered DLTs.

Grade is determined according to CTCAE v4.0.

① Hematologic toxicity of Grade 4 or higher lasting for more than 7 days^*1^.

*1 "Febrile neutropenia" is defined as Grade 3 or higher regardless of duration, and "Neutropenia" is defined as treatment with G-CSF even if it is Grade 3 or lower. Lymphocytopenia" and "CD4 lymphocytopenia" are excluded.

② Non-hematologic toxicity of Grade 3 or higher

Symptoms judged to be "injection-related reactions" ("fever," "headache," "pain," "pruritus," "allergic reaction/hypersensitivity," etc.) are defined as Grade 4 or higher DLT. In addition, only AST (GOT), ALT (GPT), ALP, total bilirubin, creatinine, and potassium should be included in the clinical examination.

③ Others

i) Toxicity that caused the scheduled administration of the investigational drug to exceed 2 weeks beyond the specified scheduled administration date due to a Grade 3 in any of the symptoms judged to be "infusion-related reactions" in 2).

ii) Toxicities other than the above that prevented administration of the study drug more than twice during the DLT observation period due to the same event.

(2) Pharmacokinetics

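### The protocol summary and section 7-7 disagree on when hydrocortisone is given, and 7-7 read literally names no steroid for the first infusion

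*Protocol*

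**What the plan says.** Both versions of the premedication paragraph start alike: diphenhydramine 30-50 mg and acetaminophen 300-500 mg, 30 minutes before study drug, because infusion reactions are expected in nearly everyone. They part on the steroid.

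- Protocol summary, section 5 (Dosing regimen): "Hydrocortisone 100 mg is also administered intravenously pre-dose; after the second dose, diphenhydramine 30-50 mg and acetaminophen 300-500 mg are administered pre-dose".
- Section 7-7 (Dosing methods): "In addition, 100 mg of hydrocortisone should be administered intravenously before the second dose of diphenhydramine 30-50 mg". The sentence then adds acetaminophen and refers to the time after the first dose.

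The clauses on discretion also differ. The summary says "Drugs or doses may be changed or increased or decreased as appropriate according to age, symptoms and other factors"; section 7-7 says only "Dosage may be adjusted according to age and symptoms".

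Three other places bear on the point:

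- Section 4-1, criterion 8, limits entry to "Patients who are able to be hospitalized for the administration of Mogamulizumab from before the first dose until the day after the first dose". Its rationale reads "Established to ensure the safety of subjects in the event of an injection-related reaction".
- Section 7-9 gives a general permission: "Corticosteroids may be administered locally or systemically as pretreatment for administration of the investigational drug".
- Section 8-3-1 sets a high bar for dose-limiting toxicity (DLT). Symptoms judged to be infusion reactions "are defined as Grade 4 or higher DLT". A Grade 3 reaction counts only if it delays dosing by more than 2 weeks.

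**The concern.** This is a bedside drug order for a reaction that the protocol expects in almost all patients. The summary implies steroid cover at infusion 1 and none named later. Section 7-7, taken word for word, does roughly the reverse: it ties the steroid to the second premedication and leaves infusion 1 with antihistamine and acetaminophen alone. Infusion 1 is also the one the protocol guards by hospitalisation.

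A site working from 7-7 could leave out the steroid at that infusion while a site working from the summary gives it. At stake are the protection of patients at first exposure and a common premedication regimen across sites and dose groups.

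**Working it through.** **1. The two instructions by infusion**

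| | Summary, section 5 | Section 7-7, read literally |
|---|---|---|
| Infusion 1 | diphenhydramine, acetaminophen, hydrocortisone 100 mg IV | diphenhydramine, acetaminophen; no steroid named |
| Second premedication | diphenhydramine, acetaminophen | hydrocortisone 100 mg IV tied to diphenhydramine and acetaminophen |
| Discretion | drugs or doses | dosage only |

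The summary column rests on its natural reading. It never says outright that the steroid belongs to infusion 1, and its reference to the second dose could mean from infusion 2 or from infusion 3. Copying the summary into 7-7 word for word would therefore not remove all doubt.

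**2. Does another section decide it?** No. Section 7-9 allows steroid pretreatment without a dose or an infusion number. Section 10-5-1 covers stopping or slowing the infusion once a reaction occurs, not its prevention.

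**3. How many patients the order covers.** From section 7-6, Phase Ia has at most 18 and Phase Ib at most 40: 18 + 40 = 58.

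**4. Could it move the dose-escalation decision?** The documents give no estimate of what hydrocortisone does to reaction rates, so a shift cannot be calculated. An upper bound on the whole contribution of infusion reactions can.

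Inputs, from section 10-4 (2), on the two earlier Japanese studies:

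- any grade: 37/43 = 86.0%
- Grade 3 or higher: 1/43 = 2.33%, exact (Clopper-Pearson) 95% CI 0.06% to 12.3%

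Assumptions: this rate carries over to solid tumours, and every reaction of Grade 3 or higher counts as a DLT. The second overstates the risk, given the rule in section 8-3-1.

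- At least 1 DLT in the first 3 patients, which adds three patients: 1 − (1 − p)³. With p = 1/43, 1 − (42/43)³ = 6.8%.
- At least 3 DLTs in 6 patients, the criterion for the maximum tolerated dose (MTD): P(X ≥ 3), X ~ Bin(6, p). With p = 1/43, 0.02%.

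| p | at least 1 of 3 | at least 3 of 6 |
|---|---|---|
| 0.06% (lower limit) | 0.2% | under 0.01% |
| 2.33% (estimate) | 6.8% | 0.02% |
| 12.3% (upper limit) | 32.5% | 2.8% |

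These figures describe all severe infusion reactions, not the effect of omitting the steroid. They show only that the MTD decision is unlikely to turn on this point.

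**The case against.** The strongest reply is that this is a translation slip and not a second schedule. The 7-7 sentence contains the same parts as the summary, run together ungrammatically, and the text reads as an English rendering of a Japanese original. Similar damage appears elsewhere: section 7-9 has vaccines to be given concomitantly where the summary asks for caution. On this view the literal reading is one parse among several. The second dose named in 7-7 is strictly a dose of diphenhydramine, and the opening words could simply add hydrocortisone to the general premedication. The summary needs a small repair too, so repairing both evenly would make them agree. Nothing in the protocol says that 7-7 overrides the summary.

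Much of this stands. The intended regimen is most likely that of the summary, and no one need have chosen a second schedule. The practical harm is also limited: antihistamine and acetaminophen are given on either reading, 7-9 allows a steroid, patients are in hospital for the first dose, vital signs are taken repeatedly during each infusion (9-5-2), and reactions prompt consideration of stopping or slowing the infusion.

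It does not remove the point. The 7-7 text is a complete sentence in the section headed dosing methods, not a gap left by text extraction. A reader who must guess or query a drug order has not been given a clear one. If the source-language text is sound, the correction is simply easier.

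**Conclusion.** The concern holds as a wording defect in a live dosing instruction. The two statements cannot both be followed as written, and no other section decides between them. The weight is minor to moderate: it is a matter of patient safety and regimen consistency at the first infusion. Divergent practice between sites is possible but not shown, and no change in reaction or DLT rates is claimed.

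No stated sample size, error rate or analysis is affected. Even on the upper-bound assumption, severe infusion reactions alone would meet the MTD criterion with probability 0.02%, at most 2.8% across the confidence interval. Confidence is medium, because the intended schedule is inferred from the summary and the 7-7 sentence is plainly garbled.

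**What to change.** Put one identical statement in the summary, section 5, and in section 7-7, naming the infusions. Unless the investigators intend otherwise:

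- before infusion 1: hydrocortisone 100 mg IV, diphenhydramine 30-50 mg and acetaminophen 300-500 mg;
- from infusion 2 onward: diphenhydramine 30-50 mg and acetaminophen 300-500 mg.

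Follow it in both places with a single flexibility clause that says whether drugs, doses or both may be changed. Check the wording against the source-language protocol when doing so.

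The cost is one corrected sentence and its copy. Section 9-3 already requires all concomitant medication to be recorded from Week 1, so data collection, sample size and analysis stay as they are.

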**7-7-1. Dosing criteria**

Patients must have had no more than Grade 3 adverse hematologic events^*1^ and no more than Grade 2 adverse non-hematologic events^*2^ prior to administration on the day of administration^*3^.

*1 "Febrile neutropenia" should not have occurred. Lymphocyte count decreased" and "CD4 lymphocyte decreased" are also excluded.

*2 Laboratory tests should be related to AST (GOT), ALT (GPT), ALP, total bilirubin, creatinine, and potassium only.

*3 If a clinical examination cannot be performed prior to the day of administration, a clinical examination performed within 3 days prior to administration may be substituted (or the most recent clinical examination if performed more than once during this period). Symptoms and findings must be confirmed prior to administration on the day of administration.

**7-7-2. Dosing deferral criteria**

Dosing of the investigational drug will be postponed if any of the following conditions occur on the scheduled dosing date^*1^. The period of postponement shall be a maximum of 2 weeks from the scheduled administration date.

1) Grade 4 or higher hematological adverse events. However, "febrile neutropenia" must be Grade 3 or higher.

2) Nonhematologic adverse events of Grade 3 or higher (excluding skin disorders). However, regarding laboratory tests, only those related to AST (GOT), ALT (GPT), ALP, total bilirubin, creatinine, and potassium should be considered.

3) In the case of ongoing skin disorders

4) If the subject requests a postponement of administration

5) Other cases in which the investigator determines that administration should be postponed

*1 Including within 3 days of the scheduled administration date as specified in the regulations.

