**7-7-3. Dose discontinuation criteria**

Dosing of the subject will be discontinued if any of the following criteria are met

1) When dosing is postponed for more than 2 weeks from the scheduled dosing date according to the criteria for dose postponement.

2) When "PD" is observed in the overall efficacy in the evaluation of RECIST variant after Week 24.

3) When a skin disorder of Grade 3 or higher is observed

4) Adverse events that make it difficult for the investigator to continue the study

5) The subject requests discontinuation of the investigational drug

6) The subject is found to be ineligible

7) Other cases in which the investigator determines that the study should be terminated.

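### Section 7-7-2 omits the lymphopenia exemption given in 7-7-1, so isolated Grade 4 lymphopenia meets the dosing criterion yet must be deferred

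*Protocol*

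**What the plan says.** Section 7-7 makes the dosing rules cumulative. Each administration must meet 7-7-1 and must be one that "does not conflict with the '7-7-2. Postponement of Administration Criteria" (and likewise for the discontinuation criteria in 7-7-3).

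- **7-7-1, dosing criteria:** "Patients must have had no more than Grade 3 adverse hematologic events" before administration on the day. Note *1 deals with febrile neutropenia and then says that decreased lymphocyte count and "CD4 lymphocyte decreased' are also excluded".
- **7-7-2 item 1, deferral criteria:** the dose is postponed for "Grade 4 or higher hematological adverse events. However, 'febrile neutropenia' must be Grade 3 or higher". Febrile neutropenia is the only qualifier. The section's single footnote concerns the 3-day window before dosing.
- **7-7-2, length of deferral:** "The period of postponement shall be a maximum of 2 weeks from the scheduled administration date".
- **7-7-3 item 1, discontinuation:** "When dosing is postponed for more than 2 weeks from the scheduled dosing date according to the criteria for dose postponement".
- **7-7, dosing interval:** "The dosing interval should not be shortened until 8 doses have been administered".
- **8-3-1, haematological DLT criterion:** lymphocytopenia and "CD4 lymphocytopenia' are excluded".

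Section 10-4 (3) lists decreased lymphocyte count under haematologic toxicity, so 7-7-2 item 1 covers it.

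**The concern.** Three parallel rules deal with haematological toxicity: the criterion to dose, the criterion to defer and the DLT definition. Two of them set lymphopenia aside and the deferral rule does not. A patient whose only abnormality on a dosing day is Grade 4 lymphopenia is acceptable under 7-7-1 and must be postponed under 7-7-2.

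This is not a rare corner case by type of event. Lymphopenia is the most common reaction listed in section 1-4 and the leading Grade 3 or higher haematological event in section 10-4. It is also close to the drug's intended action, which is to deplete CCR4-positive T cells.

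At stake is adherence to the weekly 8-dose course on which safety, pharmacokinetics and regulatory T-cell removal are assessed. Investigators who follow 7-7-2 will delay doses for an effect that 7-7-1 says should not count. Investigators who rely on note *1 will dose and commit a protocol violation.

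**Working it through.** **1. The rules side by side, for isolated lymphopenia on a dosing day**

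| Grade | 7-7-1 if it had no exemption | 7-7-1 with note *1 | 7-7-2 item 1 | Joint result |
|---|---|---|---|---|
| 3 or lower | met | met | not triggered | dose |
| 4 | not met | met | triggered | postpone |

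The note changes the 7-7-1 entry only in the Grade 4 row, and in that row 7-7-2 overrides it. The joint result is the same with or without the note, so the exemption has no effect.

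**2. Is the omission likely to be deliberate?** Section 7-7-2 otherwise carries over the qualifiers of 7-7-1. Febrile neutropenia reappears in item 1. The restriction to six laboratory tests (AST, ALT, ALP, total bilirubin, creatinine, potassium) reappears in item 2. Only the lymphocyte exemption is missing. If 7-7-2 had been meant to be stricter, the exemption in 7-7-1 would serve no purpose.

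**3. How common is the event?** The inputs are the two earlier Japanese studies summarised in sections 1-3-2 and 10-4, with 16 + 27 = 43 patients. Grade 3 or higher:

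- lymphocytes 30/43 = 69.8%
- white cells 10/43 = 23.3%
- neutrophils 8/43 = 18.6%
- platelets 5/43 = 11.6%

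Lymphopenia of any grade occurred in 41/43 = 95.3%.

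The protocol does not give Grade 4 separately. In these patients it lies between 0/43 and 30/43, that is 0% to 69.8%.

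The dose mix also limits transfer to this trial. At 1.0 mg/kg there were 6 + 27 = 33 patients (33/43 = 76.7%). At 0.01 to 0.5 mg/kg there were 16 − 6 = 10 (23.3%). All had ATL or PTCL, whereas this trial enrols solid tumours and one planned Phase Ib arm receives 0.1 mg/kg.

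**4. What one deferral does to the schedule.** With dose 1 on day 1, weekly doses fall on days 1, 8, 15, 22, 29, 36, 43 and 50. The maximum deferral is 14 days and intervals may not be shortened before dose 8, so the delay carries through to every later dose of the course: dose 8 moves to day 50 + 14 = day 64.

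Section 9-4-2 sets a regulatory T-cell sample at week 9, drawn before dosing on a dosing day. If week 9 is counted by calendar from dose 1 (an assumption), it begins on day 57. A patient with one full deferral would then have dose 6 on day 50 and dose 7 on day 57, so that sample would follow six doses instead of eight.

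**The case against.** **The joint rule is determinate and cautious.** Section 7-7-1 is a necessary condition, not an order to dose. When both sections must be satisfied, the stricter one governs and the answer is to defer. This stands: dosing is never undecidable. It does not explain why 7-7-1 contains an exemption that cannot operate.

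**Note *1 can be read another way.** The words about lymphocytes follow a statement that febrile neutropenia should not have occurred, so one could read them as a further prohibition. That reading is implausible. The DLT footnote in 8-3-1 uses parallel wording as an exemption, and the prohibition would bar dosing for an effect seen in 41/43 earlier patients. It would also still clash with 7-7-2, which defers only from Grade 4.

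**The DLT exemption is weak evidence of intent.** DLT counting sets the MTD, while deferral protects a patient on the day, so excluding an event from one and acting on it in the other can be coherent. This is fair. The case rests mainly on 7-7-1 itself and on the qualifiers that 7-7-2 did carry over.

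**The practical effect is not shown.** No Grade 4 rate, duration, dosing-day frequency or solid-tumour rate is given. Section 10-4 reports that blood-count events recovered, except in patients whose follow-up was judged unnecessary. Day 64 is the latest date after one full deferral, and discontinuation needs more than 2 weeks of postponement. All of this stands and limits the claimed size.

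**Removing an automatic pause has a safety side.** Section 7-1 expects stronger immune and autoimmune responses in solid tumours, and section 10-4 asks for infection precautions. This is a reason to keep investigator discretion, which 7-7-2 item 5 and 10-5-5 do. It is not a reason to leave two sections that disagree.

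**Conclusion.** The concern holds. As written, the lymphopenia exemption in 7-7-1 has no effect, and isolated Grade 4 lymphopenia, a severe form of the drug's most frequent reaction, triggers mandatory postponement. The direct cost is a delay of up to 14 days per deferral, carried through to the later doses of the 8-dose course. A permanent stop follows only if postponement exceeds 2 weeks, and the protocol does not document how often Grade 4 lasts that long.

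The number of patients affected cannot be estimated: the source data allow 0% to 69.8% for Grade 4 at any time, in a different disease and mostly at 1.0 mg/kg. The conclusion rests on reading note *1 as an exemption, which the wording of 8-3-1 and the 41/43 frequency support. It should be fixed, but it does not threaten the design.

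**What to change.** Add one sentence to 7-7-2 item 1 stating that decreases in lymphocyte count and in CD4 lymphocytes do not count, matching 7-7-1 note *1. Lymphopenia alone then causes no automatic deferral. An investigator who is concerned can still postpone under 7-7-2 item 5 or act under 10-5-5. The DLT definition stays as it is.

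If the investigators do want Grade 4 lymphopenia to defer dosing, they should instead delete the exemption from 7-7-1 and say so. The text points to the first option, but either way the two sections must agree.

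The cost is a one-sentence protocol amendment, with no extra patients or tests. The downside is that patients with Grade 4 lymphopenia continue weekly dosing unless the investigator holds the drug.
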